### Sample size calculation

The primary outcome of this study is the postoperative VAS score. In accordance with the pre-experimental results, there will be no severe postoperative pain until 1 h after the surgery. Therefore, sample size was calculated based on the VAS score at 1 h after the ESD procedure. The mean VAS at 1 h in TEAS group and the sham group in the pre-experiment was 0.86 ± 1.14 and 1.68 ± 1.46, respectively. The PASS 11.0 software was used, with unilateral α = 0.05, β = 0.1 and power = 0.90. A total of 55 effective samples were estimated for each group. Considering of 10% patient loss, we set 60 cases for each group in this study. Eventually, we will involve 120 cases, including 60 patients in the TEAS group and 60 patients in the control group (30 in esophageal ESD and 30 in gastric ESD procedure). Our digestive endoscopy center performs 300–400 upper gastrointestinal ESD surgeries, so this trail period is set at 16 months consequently.

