### Randomization and blinding

This is a single-blinded study. To minimize evaluation bias, the evaluators responsible for screening and outcome evaluation will be blinded to the grouping information. The anesthesiologist, and the acupuncturist who is in charge of the TEAS stimulation from the traditional Chinese department, will acknowledge each patient’s affiliation, but will be isolated to the research results. Patients will not be informed about their group assignment. Randomization will be performed by a computer-generated blocked randomization order. A nurse will generate the allocation sequence and prepare the sealed, numbered envelops. Each envelop will be unfolded by the anesthesiologist until the patient entering the operating room. Subjects will be randomly assigned to the sham group or the TEAS group with a ratio of 1:1 by the anesthesiologist according to these envelops. The case report forms (CRF) will be used to record all the original data needed.

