### Statistical analysis

Statisticians will negotiate with the research team to establish statistical analysis plans, develop databases, and perform statistics with the SPSS statistical analysis system. Statistics analyses include demographic and other baseline characteristics, postoperative pain degree analysis, statistical analysis of recovery time of gastrointestinal function, the incidence of complications and combined treatments, and comprehensive efficacy evaluation. Statisticians will use mean ± standard deviation (SD) to express measurement data that meet the normality test and use t-test to analyze. Non-parametric measurement data will be described as median and interquartile range (IQR), and Wilcoxon signed rank test will be applied. Enumeration data will be expressed as numbers and percentages. Pearson’s chi-squared test and Fisher’s exact test will be the methods applied for these data. Univariate logistic regression analysis will be applied to analyze risk factors which are reported to have possible correlation with VAS ≥ 4 in previous studies. Variables which are considered statistically significant (*P* < 0.05) will be selected for multivariable logistic regression to explore the association of those with post-ESD VAS ≥ 4. The Hosmer-Lemeshow test will be used to evaluate goodness-of-fit of the model. All *P* values above are unilateral and *P* < 0.05 will be considered significant. Subgroup analysis will be conducted in accordance with different procedure types. Intention to treat (ITT) principle will be applied to analyze all data. Because all the data will be collected during hospital stay by a conscientious observer (except for the last entry of QLQ-C30 life quality scale, which will be completed at a month after surgery), missing data can be mostly avoided. The mean imputation method will be used if missing data still preserves. The Capital Medical University statistical department will determine detailed analyzing methods for the main efficacy indicators.

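### The 55 per group does not follow from the stated one-sided alpha of 0.05, which needs 45; it fits a two-sided 0.05 test, while the analysis judges every P value one-sided at 0.05

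*Protocol article*

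**What the plan says.** All references are to the protocol article.

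- **Sample size calculation, endpoint:** "sample size was calculated based on the VAS score at 1 h after the ESD procedure".
- **Sample size calculation, pilot data:** "The mean VAS at 1 h in TEAS group and the sham group in the pre-experiment was 0.86 ± 1.14 and 1.68 ± 1.46, respectively".
- **Sample size calculation, error rates:** the PASS run is described as "with unilateral α = 0.05, β = 0.1 and power = 0.90".
- **Sample size calculation, result:** "A total of 55 effective samples were estimated for each group". This is raised to 60 per group for a 10% loss, 120 in total.
- **Randomization and blinding:** allocation is 1:1.
- **Statistical analysis:** a t-test is planned for normally distributed measurements. The section also names a Wilcoxon test, Pearson's chi-squared, Fisher's exact test, univariate and multivariable logistic regression, and the Hosmer-Lemeshow test. After listing these it says that all P "values above are unilateral and" sets the threshold at P < 0.05.

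No section mentions a two-sided test or a one-sided level of 0.025.

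**The concern.** Every input to the sample size is printed, so the result can be checked, and it does not come out. The gap is 10 patients per group (55 against 45). Rounding, or the choice between a normal and a t calculation, moves the answer by only one. At least one input is therefore misreported, and sidedness is the obvious candidate.

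Sidedness matters beyond the sample size because the same word governs the analysis. If 55 came from a two-sided calculation, the trial recruits enough patients for a two-sided 0.05 test and then declares success on a looser rule. The chance of wrongly declaring TEAS better is then 5% per test, against 2.5% in that direction under the two-sided rule.

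The blanket one-sided rule also covers tests it does not fit. Hosmer-Lemeshow and chi-squared tests on tables larger than 2×2 have no directional alternative. For complications and for risk factors for VAS ≥ 4, no direction is given, so a one-sided P value is undefined until someone chooses one, possibly after seeing the data.

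**Working it through.** **Inputs (Sample size calculation; allocation from Randomization and blinding).** Difference = 1.68 − 0.86 = 0.82. Variances: 1.14² + 1.46² = 1.2996 + 2.1316 = 3.4312. Root-mean-square SD = √(3.4312/2) = 1.310. Power 0.90, 1:1 allocation.

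**Formula.** Normal approximation, per group: n = (z_α + z_β)² × (SD₁² + SD₂²) / difference². The t-test figure is the smallest n at which noncentral-t power reaches 0.90.

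**Step 1: the plan's figure from its stated inputs (one-sided 0.05).**
(1.645 + 1.282)² × 3.4312 / 0.82² = 43.7, so 44 by the normal approximation. By t-test, 44 gives power just under 0.90 (0.898) and 45 gives 0.904 (0.903 with Welch degrees of freedom). The requirement is **45**. The stated 55 is not reproduced; at 55 the one-sided power is 0.947.

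**Step 2: the same inputs, two-sided 0.05.**
(1.960 + 1.282)² × 3.4312 / 0.82² = 53.6, so 54 by the normal approximation. By t-test, 54 gives 0.897 (0.896 with Welch) and 55 gives 0.902. The requirement is **55**, an exact match.

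**Step 3: other routes to 55.**

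| Calculation, 90% power | n per group |
|---|---|
| One-sided 0.05, printed SDs, t-test | 45 |
| One-sided 0.05, Mann-Whitney allowance (efficiency 3/π) | 45/0.955 = 47.1 |
| One-sided 0.05, Mann-Whitney worst case (efficiency 0.864) | 45/0.864 = 52.1 |
| One-sided 0.05, SD 1.46 in both groups | **55** (power 0.9001) |
| Two-sided 0.05, printed SDs, t-test | **55** (power 0.902) |
| Two-sided 0.05, SD 1.46 in both groups | 68 |

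Two routes reach 55. The two-sided route keeps every printed mean and SD and changes only the sidedness. The one-sided route keeps the sidedness but replaces the printed TEAS SD of 1.14 with 1.46.

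**Step 4: loss to follow-up.** 55/(1 − 0.10) = 61.1, so 62 per group would be needed to keep 55. The planned 60 leaves 60 × 0.90 = 54.

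**Step 5: power with 54 evaluable per group (t-test, printed SDs).** One-sided 0.05: 0.944. Two-sided 0.05: 0.897. With all 60 evaluable, the two-sided power is 0.925.

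**The case against.** The best defence has four parts.

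- **The cause is not proven.** A reader might infer that 55 can only be the two-sided answer. The documents do not support that: one-sided 0.05 with SD 1.46 in both groups also gives 55, and the article reports neither route. This stands. What can be said is that 55 does not follow from the inputs as printed, and that the two-sided route fits best.
- **The two sections agree on sidedness, and the hypothesis is directional.** Both sections say one-sided 0.05, the level is stated in advance, and the Abstract and Discussion frame the question as TEAS being superior to sham. This is correct: the contradiction lies between alpha and n within the sample size section. The 5% against 2.5% comparison is with the conventional two-sided level, which the article does not adopt. It still carries weight, because the planned size already supports the stricter test and the article gives no reason for the looser one.
- **Some of the listed tests do have one-sided forms.** Logistic coefficients, Fisher's exact test and 2×2 comparisons can be tested directionally. The rule fails outright only for Hosmer-Lemeshow and for larger chi-squared tables. A reader might also infer that the rule makes harm impossible to declare. The article does not show that: it leaves the direction for complications unspecified, adverse events are assessed individually (Safety), and the monitoring committee weighs safety (Data collection methods and monitoring).
- **The trial is large enough.** This stands too. A reader might take the mismatch to mean an underpowered trial, but 55 exceeds the 45 that the stated inputs require. The dropout slip costs about half a percentage point of two-sided power.

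**Conclusion.** The point holds. The sample size statement is wrong as written: its inputs give 45 per group, not 55, and 55 corresponds to 94.7% power rather than 90%. Two-sided 0.05 is the best-fitting source of the 55, but this remains an inference until the PASS output is seen.

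The decision rule in Statistical analysis is looser than the planned size supports, at 5% rather than 2.5% error per test in favour of TEAS. It cannot be applied to Hosmer-Lemeshow or to chi-squared tests on tables larger than 2×2, and it is undefined for complications and risk factors. The article itself fixes this rule, so it is not a detail left to an unseen analysis plan.

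The dropout step is a minor slip: 54 evaluable per group, not 55. With 54 and the printed SDs, power is 94.4% one-sided and 89.7% two-sided, so the number of patients is not in question.

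These figures assume the 1 h VAS endpoint, the printed pilot means and SDs, 1:1 allocation and a t-test.

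**What to change.** 1. Retrieve the PASS output and correct whichever input the Sample size calculation section misreports. If a common SD of 1.46 was used, say so.
2. State two-sided alpha 0.05 in that section. In Statistical analysis, replace the one-sided rule with two-sided P < 0.05 for all tests; tests with no direction, such as Hosmer-Lemeshow, then need no special handling.
3. Restate the power as about 90% (89.7%) with 54 evaluable per group from 60 randomised at 10% loss.

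Cost: no extra patients with the printed SDs. The significance threshold becomes stricter. The change is a protocol amendment during recruitment: Trial status reports 70 participants included and the trial ongoing. It should be made before results are known. One condition applies: if the output shows that SD 1.46 in both groups was the deliberate planning value, 90% power two-sided would need 68 per group. The 89.7% then could not be claimed on that SD, and the authors would have to say which SD they stand behind.

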### Statistical analysis

Statisticians will negotiate with the research team to establish statistical analysis plans, develop databases, and perform statistics with the SPSS statistical analysis system. Statistics analyses include demographic and other baseline characteristics, postoperative pain degree analysis, statistical analysis of recovery time of gastrointestinal function, the incidence of complications and combined treatments, and comprehensive efficacy evaluation. Statisticians will use mean ± standard deviation (SD) to express measurement data that meet the normality test and use t-test to analyze. Non-parametric measurement data will be described as median and interquartile range (IQR), and Wilcoxon signed rank test will be applied. Enumeration data will be expressed as numbers and percentages. Pearson’s chi-squared test and Fisher’s exact test will be the methods applied for these data. Univariate logistic regression analysis will be applied to analyze risk factors which are reported to have possible correlation with VAS ≥ 4 in previous studies. Variables which are considered statistically significant (*P* < 0.05) will be selected for multivariable logistic regression to explore the association of those with post-ESD VAS ≥ 4. The Hosmer-Lemeshow test will be used to evaluate goodness-of-fit of the model. All *P* values above are unilateral and *P* < 0.05 will be considered significant. Subgroup analysis will be conducted in accordance with different procedure types. Intention to treat (ITT) principle will be applied to analyze all data. Because all the data will be collected during hospital stay by a conscientious observer (except for the last entry of QLQ-C30 life quality scale, which will be completed at a month after surgery), missing data can be mostly avoided. The mean imputation method will be used if missing data still preserves. The Capital Medical University statistical department will determine detailed analyzing methods for the main efficacy indicators.

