### Trial design

This study is a single-center, prospective, single-blind, randomized, and controlled trial. A total of 120 patients undergoing elective gastric and esophageal ESD surgery in Beijing Friendship Hospital, Capital Medical University, will be stratified by the type of ESD surgery (i.e. gastric or esophageal procedure) at 1:1 ratio and be randomized into two groups: the sham group (Group S, *n* = 60) and the TEAS treatment group (Group T, *n* = 60). Each group has 30 gastric cases and 30 esophageal cases (Fig. 1). The observers will conduct screening according to the pre-standard plan. Data gathering will start from the collection of basic data and last until the end of follow-up (Table 1). According to the hospital regulations, compensation and post-trial care will be provided to those injured due to their participation in the trial.

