### Outcomes

#### Primary outcome

The primary outcome is post-operative pain (VAS) score at the time of entering PACU, 10 min, 20 min, 30 min, 1 h, 2 h, 4 h, 6 h, 18 h, 24 h, 48 h after the surgery. The incidence of post-ESD VAS ≥ 4 and the consumption of morphine during follow-up will also be recorded.

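### The plan names a paired test (Wilcoxon signed rank) for non-normal data, although it compares two independent randomised groups

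*Protocol article*

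**What the plan says.** The Trial design section says patients will "be randomized into two groups: the sham group (Group S, *n* = 60) and the TEAS treatment group (Group T, *n* = 60"). Randomization and blinding confirms this: "Subjects will be randomly assigned to the sham group or the TEAS group with a ratio of 1:1". Neither section describes matching, crossover or a within-patient treatment contrast.

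The Statistical analysis section sorts measurement data by a normality test. If the data pass: "Statisticians will use mean ± standard deviation (SD) to express measurement data that meet the normality test and use t-test to analyze". If they do not: "Non-parametric measurement data will be described as median and interquartile range (IQR), and Wilcoxon signed rank test will be applied". No other test is named for non-normal measurement data; neither the rank-sum nor the Mann-Whitney test appears in the article. The same section makes all P values one-sided at 0.05. It ends by leaving the detailed methods for the principal efficacy measures to the university's statistical department.

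On the outcome: "The primary outcome is post-operative pain (VAS) score at the time of entering PACU" and at ten later times up to 48 h. The Sample size calculation section works from the 1 h value: "The mean VAS at 1 h in TEAS group and the sham group in the pre-experiment was 0.86 ± 1.14 and 1.68 ± 1.46, respectively".

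**The concern.** The signed rank test ranks differences within pairs. A TEAS patient and a sham patient do not form a pair, and stratifying by gastric or esophageal procedure does not make them one. Anyone following the text must either invent a pairing, in practice the row order of the data file, or find that the test does not run because the arms differ in size.

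This could be dismissed as a detail of a fallback branch. But the t-test is allowed only for data that pass the normality test, and the pilot figures suggest that the 1 h VAS will not pass. The stated rule would then send the VAS on which the trial is sized to a test that does not fit the design. Times to first flatus, defecation, drinking and solid diet, hospital stay and costs are typically skewed and fall under the same rule.

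**Working it through.** **1. Does the sample size imply pairs?** Inputs from Sample size calculation: difference 1.68 − 0.86 = 0.82; mean variance (1.14² + 1.46²)/2 = (1.2996 + 2.1316)/2 = 1.7156, so SD 1.31. Independent-groups formula: n per group = 2 × variance × (z_alpha + z_beta)² / difference².

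- Two-sided 0.05, power 0.90: 2 × 1.7156 × (1.960 + 1.282)² / 0.6724 = 53.6, so 54; with the t distribution, 55.
- One-sided 0.05, power 0.90: 2 × 1.7156 × (1.645 + 1.282)² / 0.6724 = 43.7, so 44; with the t distribution, 45.

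The stated 55 matches an independent two-sample calculation (two-sided, although the text says one-sided; that is a separate matter). No within-pair correlation or SD of differences is given, so nothing in the planning assumes pairs.

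**2. Will the 1 h VAS reach the non-normal branch?** VAS cannot fall below 0. SD/mean is 1.14/0.86 = 1.33 (TEAS) and 1.46/1.68 = 0.87 (sham). Share of a normal distribution below 0:

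- TEAS: Phi(−0.86/1.14) = Phi(−0.754) = 22.5%
- Sham: Phi(−1.68/1.46) = Phi(−1.151) = 12.5%

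Simulated integer scores from 0 to 10 with moments close to these (negative binomial or rounded gamma, both assumed shapes) failed Shapiro-Wilk in both arms in all 1,000 trials checked per setting, at 55 and at 60 per arm.

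**3. What does arbitrary pairing do on average?** Negative binomial scores, 60 per arm, one-sided 0.05, 4,000 simulated trials:

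| | Rank-sum | Signed rank, arbitrary pairs |
|---|---|---|
| Type I error | 0.048 | 0.050 |
| Power | 0.975 | 0.965 |

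The two tests gave the same verdict in 98% of trials. Over both assumed shapes and 55 or 60 per arm (3,000 trials each), one-sided power was 0.965 to 0.990 for rank-sum and 0.950 to 0.975 for signed rank.

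**4. What does it do to a single data set?** The data were held fixed and the rows re-ordered 1,000 times.

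- Two-sided rank-sum P = 0.085 (one-sided 0.085/2 = 0.0425, significant under the plan). The two-sided signed rank P ran from 0.015 to 0.221, and 71% of orderings were significant at one-sided 0.05.
- Two-sided rank-sum P = 0.077 (one-sided 0.077/2 = 0.0385, also significant). Only 17% of orderings were significant at one-sided 0.05.

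Across borderline data sets the share of significant orderings ran from 5% to 100%. Far from the threshold the P value still moves, for example from 0.000008 to 0.004 in one simulated trial, but the verdict does not.

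**5. Unequal arms.** With 55 values in one arm and 57 in the other, the signed rank routine stops with an error.

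**The case against.** **It is probably a slip of the pen.** The sentence runs parallel to the one giving the t-test for two groups, and the sample size is an independent two-sample one. That is the likeliest explanation and it makes the repair easy, but the published text still prescribes the wrong test.

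**The statistical department will settle the details.** It may well correct this for the primary VAS. But the deferral does not withdraw the named test, and it covers only the principal efficacy measures. The secondary measures remain under the stated rule.

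**The test suits within-patient change**, such as QLQ-C30 before and after surgery. It would, but the section describes no such comparison and assigns the test to all non-normal measurement data.

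**The consequences are easily overstated.** This stands in three respects.

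- A reader might infer that the P value would have nothing to do with the data. It would not be detached from them: type I error is held, power falls by about one point at 60 per arm in the main simulation, and verdicts agree in 98% of trials. The P value is partly arbitrary.
- A reader might infer that the primary analysis cannot be run. That is conditional. The plan is for 60 and 60, with intention-to-treat analysis and mean imputation, so the arms may be equal. The discharge criteria, or a stop at the mid-trial review, could make them unequal, but neither is certain.
- A reader might take it as established that the VAS will fail the normality test. The article does not name the normality test or say whether VAS is recorded in whole points, and the 100% rejection rate rests on assumed distributions.

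**Conclusion.** The point holds as an error in the stated method: a paired test is prescribed for all non-normal measurement data in a trial of two independent groups. It very probably reaches the 1 h VAS, because the pilot means and SDs are hard to reconcile with normality on a scale bounded at 0. Non-normality is inferred from those figures; the article does not state it.

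The harm is to validity and reproducibility, with little effect on average error rates. In borderline data the order of the rows can decide whether one-sided P falls below 0.05, and a confirmatory comparison should not offer that freedom. Such data would be uncommon if the pilot effect is real and more relevant if the true effect is smaller. The simulation figures depend on assumed count-type or rounded-gamma scores and illustrate the size of the problem; they do not predict this trial's result.

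**What to change.** In Statistical analysis, replace the signed rank test with the Wilcoxon rank-sum (Mann-Whitney U) test for between-group comparisons of non-normal measurement data, and carry the same wording into the statistical analysis plan. If within-patient changes are also to be tested, say so and keep the signed rank test for those only. A version stratified by procedure type (van Elteren) would match the stratified randomisation but is optional.

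The cost is one phrase, with no extra patients or data and no stated figure changed. Timing matters: the Trial status section reports 70 participants included, and the data monitoring committee is to unblind and weigh effectiveness mid-trial. The correction should be made and dated before any unblinded data are seen.

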According to previous studies results, female gender, long operation time, lesion location and acid allergy are the potential risk factors of post ESD pain [4, 18, 19]. Although without fully understanding of the mechanism of the post ESD pain, some studies shows that it may be associated with residual mucosal defects (dropsical and inflamed artificial ulcers), transmural burns and air leaks [23, 24], acid sensitivity [19], or the penetration or chemistry of submucosal fluid injections [4]. Besides that, severe inflammatory reaction [25] and pulling of inflammatory tissue [19] may also be the mechanism of pain development, as well as bile acid reflux [26] and gas expansion [18] after ESD. Based on the factors and mechanisms above, we need to explore suitable postoperative analgesia for ESD surgery patients and to give preventive and early analgesic drugs for high-risk groups.

Currently, no unified conclusion is made on how to perform effective postoperative analgesia on patients with gastric and esophageal ESD surgery. Jung et al. suggested that hypersensitivity to gastric acid had large possibility to fuel the pain after ESD, and the prophylactic treatment of proton pump inhibitor (PPI) was effective in reducing pain [19]. Intravenous dexamethasone given after the ESD surgery was found helpful to alleviate epigastric postoperative pain [7]. Kim et al. proved that local infiltration treatment with bupivacaine and triamcinolone could also help relieve abdominal pain after ESD [8, 9]. Intravenous lidocaine during ESD can reduce the amount of intraoperative opioids and patients’ body movement, while relieving postoperative pain in the upper abdomen and throat [8].

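### The exploratory risk-factor model for VAS ≥ 4 chooses its variables by a univariate P < 0.05 screen, which at 120 patients drops modest true factors and inflates those that survive

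*Protocol article*

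**What the plan says.** The Statistical analysis section of the protocol article sets out two steps.

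- Step one: "Univariate logistic regression analysis will be applied to analyze risk factors which are reported to have possible correlation with VAS ≥ 4 in previous studies".
- Step two: variables with P < 0.05 "will be selected for multivariable logistic regression", with the stated purpose of exploring how they relate to VAS ≥ 4 after ESD.

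Model fit is then checked with the Hosmer-Lemeshow test. The same section states that the P "values above are unilateral and" are judged at 0.05, so the screen as written is one-sided. No other selection rule is given.

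The Discussion lists candidates from earlier work: "female gender, long operation time, lesion location and acid allergy are the potential risk factors of post ESD pain". The Sample size calculation section fixes the total: "Eventually, we will involve 120 cases, including 60 patients in the TEAS group and 60 patients in the control group". It sizes the trial on mean VAS at 1 h, and gives no event count or power for the risk-factor model.

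**The concern.** Screening on univariate significance lets the same data choose the model and estimate it. Two things follow. A real factor of modest strength often fails the screen by chance and vanishes from the model. When it passes, it tends to be because its estimate happened to be high, so the reported odds ratio is too large. The P values and intervals of the final model are computed as if the variables had been fixed in advance, so they overstate certainty. The Hosmer-Lemeshow test looks at fit and does not detect or correct this.

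The list of candidates from earlier studies is short, so there is little need to screen. At stake is the trial's published set of risk factors for post-ESD pain and the size of their odds ratios.

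**Working it through.** **Inputs from the protocol**

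- N = 120; screen at one-sided 0.05.
- Event rates cited in the Abstract, Background and Discussion: 44.9% to 62.8% for moderate to severe pain, and 36.4% needing a pain reliever. In 120 patients: 120 × 0.364 = 43.7 and 120 × 0.628 = 75.4, so about 44 to 75 events.

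**Assumptions (not in the protocol)**

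- A binary factor present in half the patients (60 and 60).
- True odds ratio 1.5, 2 or 3, in the expected direction.

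The plan has no figure of its own for this model to reproduce.

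**Step 1. Chance of passing the screen, worked once.** Take OR 2 and a 44.9% event rate. The risks that give this average are 0.364 without the factor and 0.534 with it. The expected cells are 21.8, 38.2, 32.0 and 28.0.

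- SE(log OR) = √(1/21.8 + 1/38.2 + 1/32.0 + 1/28.0) = 0.373
- P(pass) = Φ(ln 2 / 0.373 − 1.645) = Φ(0.21) ≈ 0.585, so about 41.5% are dropped.
- Smallest odds ratio that passes ≈ exp(1.645 × 0.373) = 1.85.

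With a 60/60 split the SE cannot fall below √(4/30) = 0.365. The pass mark is therefore never below exp(1.645 × 0.365) = 1.82. A balanced factor with a true OR of 1.5 can pass only with an exaggerated univariate estimate.

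**Step 2. Simulation** (200,000 trials per setting, Wald test, event rates 36.4%, 44.9%, 53.8% and 62.8%):

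| True OR | Dropped | Median OR if kept | Median OR, no screen |
|---|---|---|---|
| 1.5 | 71% | about 2.3 | 1.5 |
| 2 | 41–42% | 2.4–2.5 | 2.0 |
| 3 | 9–11% | 3.2 | 3.0–3.1 |

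**Step 3. Sensitivity at true OR 2**

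- Factor present in 30% of patients: 47–52% dropped; average OR if kept 2.8–3.0.
- Screen run two-sided at 0.05: about 52–57% dropped.
- Five true factors screened together (treatment included as one of them, by assumption): on average 2.5–2.6 of five are dropped, and all five survive in 2–3% of trials. The binary risk factors that are kept average OR 2.7–3.2 in the final model, against 2.07–2.15 in a full model without screening.
- Fewer events: at an assumed 20% rate (24 events), 56% dropped and median 3.0 if kept; at 10% (12 events), 74% and about 4.5.

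**Step 4. How low could events be?** The pilot VAS at 1 h "was 0.86 ± 1.14 and 1.68 ± 1.46, respectively" (TEAS, then sham). A normal approximation gives P(VAS ≥ 4) = 1 − Φ((4 − 1.68)/1.46) = 5.6% for sham and 1 − Φ((4 − 0.86)/1.14) = 0.3% for TEAS. Skewed distributions with the same moments give about 11% and 3–4%, or roughly 9 events in 120. These figures are for one time point, whereas VAS is scored at 11 points up to 48 h, so the rate over follow-up should be higher. The protocol does not give it.

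**The case against.** The strongest reply is that the analysis is exploratory and nothing that matters depends on it. Much of that stands, and it rules out several stronger readings.

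- A reader might infer that the treatment effect on VAS ≥ 4 could be lost if the arm fails the screen. The documents do not support this. The regression is a prognostic-factor analysis; the incidence of VAS ≥ 4 is recorded separately, and count data are compared by chi-squared or Fisher's exact test under intention to treat.
- A reader might infer from the Discussion's remark on high-risk groups that this model's output will guide care. That remark rests on the factors and mechanisms from earlier studies just reviewed there, not on this regression.
- A reader might lead with the roughly 10-event case. It comes from 1 h pilot scores only and is not the event rate the protocol cites.
- A reader might count it as an error that the arm and the stratification factor are not forced in. The article says that statistical analysis plans will be established, so that detail may be settled there.

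Effect size also matters: at an odds ratio of about 3 the screen does little harm. A full model is not free of trouble either; with about 10 events it can be very imprecise or fail to converge.

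What remains is the rule itself. It is stated, not omitted, and the article defers to the statistical department only the detailed methods for the main efficacy indicators, which this model is not. Calling an analysis exploratory does not make its odds ratios unbiased.

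**Conclusion.** The point holds as a minor one. At 120 patients and the cited event rates, the stated one-sided screen drops a balanced factor with a true odds ratio of 2 in about 42% of trials and reports a median of about 2.5 when it is kept. The harm is greater at 1.5 (about 71% and 2.3) and mild at 3 (about 10% and 3.2). The final model's P values and intervals take no account of the selection.

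The size rests on assumed odds ratios and factor prevalence, and on the event rates cited from earlier studies. It would be wrong to say that the resulting list mostly reflects chance; that holds only for modest effects or few events. The primary pain comparison and the randomised comparison of VAS ≥ 4 do not depend on this model.

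**What to change.** Delete the univariate selection step. Fit one logistic model for VAS ≥ 4, named in advance, with treatment arm, procedure type, sex and operation time. Add lesion location only if it is defined so that it does not duplicate procedure type (gastric or oesophageal), and acid sensitivity only if it is collected. Report every odds ratio with its 95% CI, label the analysis exploratory, and show univariate odds ratios descriptively only.

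At the cited rates the smaller outcome class is about 44 to 55 patients: 11 to 14 per parameter with four terms, 9 to 11 with five and 7 to 9 with six. If the number falls below about 10 per parameter, use Firth penalised likelihood or fewer terms.

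The cost is a change of wording in the analysis plan, made before the outcome data are unblinded for analysis. The downside is slightly wider intervals where a term proves uninformative, and Firth estimation may need an SPSS extension.
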